### 170 3.3 Criteria for judging the efficacy of acute leukemia

171 Evaluation of the efficacy of acute leukemia: according to the 2011 edition of "Chinese Guidelines for  
172 Diagnosis and Treatment of Adult Acute Myeloid Leukemia (Non - Acute Promyelocytic Leukemia)"  
173 and the 2012 edition of "Expert Consensus on the Diagnosis and Treatment of Adult Acute  
174 Lymphoblastic Leukemia in China". Results included the following possibilities: complete remission  
175 (morphological complete remission, molecular complete remission, morphological complete remission  
176 without complete blood count recovery), relapse (molecular/genetic relapse, hematologic relapse) .

| Clinical efficacy                                                            | Evaluation indicators                                                                                                                                                                                                    |
|------------------------------------------------------------------------------|--------------------------------------------------------------------------------------------------------------------------------------------------------------------------------------------------------------------------|
| Morphological complete remission (CR)                                        | Morphologically without leukemic status, free from transfusion, and without extramedullary leukemia. The absolute neutrophil count was $>1.0 \times 10^9/L$ , and the platelets were $>100 \times 10^9/L$ .              |
| Cytogenetic complete remission (CRc)                                         | Chromosomal return to normal karyotype after remission in patients with chromosomal abnormalities before treatment                                                                                                       |
| Molecular complete remission (CRm)                                           | Patients with specific genetic markers and immunophenotypic characteristics before treatment turned negative after treatment                                                                                             |
| Morphological complete remission without complete blood count recovery (CRi) | Meets clinical and myeloid criteria for CR but still has neutropenia ( $<1.0 \times 10^9/L$ ) or thrombocytopenia ( $<100 \times 10^9/L$ )                                                                               |
| Morphological recurrence                                                     | Recurrence of leukemia cells in the peripheral blood of CR patients, immature cells in the bone marrow $\geq 5\%$ or new pathological hematopoiesis, and morphologically verifiable leukemia cells in the extramedullary |
| Molecular/genetic recurrence                                                 | Cytogenetic or molecular abnormalities in patients who have achieved complete remission at the cytogenetic or molecular level                                                                                            |

177

### 178 3.4 Criteria for judging transplantation-related complications

179 Various toxic and side effects occurred in patients after haploid hematopoietic stem cell transplantation  
180 were observed. According to various adverse reactions that may occur after treatment, the adverse  
181 reactions were divided into 5 grades to evaluate the side effects of the treatment in this study.

| Grading criteria for adverse events in haploid hematopoietic stem cell transplantation (refer to CTCAE v4.0) |       |
|--------------------------------------------------------------------------------------------------------------|-------|
|                                                                                                              | level |

|                                           | Level 1                                                                                                     | level 2                                                                                                                                                                                                                                            | Level 3                                                                                              | level 4                                                          | Level 5 |
|-------------------------------------------|-------------------------------------------------------------------------------------------------------------|----------------------------------------------------------------------------------------------------------------------------------------------------------------------------------------------------------------------------------------------------|------------------------------------------------------------------------------------------------------|------------------------------------------------------------------|---------|
| Blood disease adverse events       |                                                                                                             |                                                                                                                                                                                                                                                    |                                                                                                      |                                                                  |         |
| Anemia                                    | Hemoglobin < lower limit of normal - 100g/L                                                                 | Hemoglobin <100-80g/L                                                                                                                                                                                                                              | Hemoglobin <80-65g/L; blood transfusion required                                                     | Life-threatening consequences; urgent medical attention required | Death   |
| Decreased lymphocyte count                | <LLN-800/mm  ; <LLN×0.8×10  /L                                                      | <800-500/mm  ; <0.8-0.5×10  /L                                                                                                                                                                                             | <500- 200/mm  ; <0.5-0.2×10  /L                                              | <200/mm  ; <0.2×10  /L                   | Death   |
| Decreased neutrophil count                | <Lower limit of normal value-1500/mm  ; <Lower limit of normal value-1.5×10  /L     | <1500- 1000/mm  ; <1.5-1.0× 10  /L                                                                                                                                                                                         | <1000- 500/mm  ; <1.0-0.5× 10  /L                                            | <500/mm  ; <0.5×10  /L                   | Death   |
| Decreased platelet count                  | <Lower limit of normal value-75,000/mm  ; < Lower limit of normal value-75.0×10  /L | <75,000-50,000/mm  ; <75.0-50.0 ×10  /L                                                                                                                                                                                    | <50,000-25,000/mm  ; <50.0-25.0 ×10  /L                                      | <25,000/mm  ; <25.0×10  /L               | Death   |
| Decreased white blood cell count          | <Lower limit of normal value-3000/mm  ; <Lower limit of normal value-3.0×10  /L     | <3000- 2000/mm  ; <3.0-2.0×10  /L                                                                                                                                                                                          | <2000-1000/mm  ; <2.0-1.0× 10  /L                                            | <1000/mm  ; <1.0×10  /L                  | Death   |
| Laboratory abnormalities           |                                                                                                             |                                                                                                                                                                                                                                                    |                                                                                                      |                                                                  |         |
| Elevated alanine aminotransferase (ALT)   | >Upper Normal - 3.0x Upper Normal                                                                           | Asymptomatic: >3.0-5.0 times the upper limit of normal; >3 times the upper limit of normal, accompanied by aggravation of the following symptoms: fatigue, nausea, vomiting, pain or tenderness in the upper right area, fever, rash, eosinophilia | >5.0-20.0 times the upper limit of normal; for more than 2 weeks, >5 times the upper limit of normal | >20.0 times the upper limit of normal                            | Death   |
| Elevated aspartate aminotransferase (AST) | >Upper Normal - 3.0x Upper Normal                                                                           | Asymptomatic: >3.0-5.0 times the upper limit of normal; >3 times the upper limit of normal with aggravation of the following symptoms: fatigue, nausea, vomiting, pain or tenderness in the upper right                                            | >5.0-20.0 times the upper limit of normal; for more than 2 weeks, >5 times the upper limit of normal | >20.0 times the upper limit of normal                            | Death   |

|                                        |                                                                                                                                       |                                                                                              |                                                                                     |                                                                                               |       |
|----------------------------------------|---------------------------------------------------------------------------------------------------------------------------------------|----------------------------------------------------------------------------------------------|-------------------------------------------------------------------------------------|-----------------------------------------------------------------------------------------------|-------|
|                                        |                                                                                                                                       | area, fever, rash, eosinophilia                                                              |                                                                                     |                                                                                               |       |
| Increased blood bilirubin              | >Upper Normal - 1.5x Upper Normal                                                                                                     | >1.5-3.0 times the upper limit of normal                                                     | >3.0-10.0 times the upper limit of normal value                                     | >10.0 times the upper limit of normal                                                         | Death |
| Increased creatine phosphokinase (CPK) | >Upper Normal - 2.5x Upper Normal                                                                                                     | >2.5 times the upper limit of normal value - 5 times the upper limit of normal value         | >5 times the upper limit of normal value - 10 times the upper limit of normal value | >10 times the upper limit of normal                                                           | Death |
| Hyperglycemia                          | Fasting glucose concentration > upper limit of normal - 160 mg/dL; fasting glucose concentration > upper limit of normal - 8.9 mmol/L | Fasting glucose concentration >160-250 mg/dL; fasting glucose concentration >8.9-13.9 mmol/L | >250-500 mg/dL; >13.9-27.8 mmol/L; hospitalization required                         | >500mg/dL; >27.8mmol/L; life-threatening                                                      | Death |
| Hypokalemia                            | <Lower limit of normal value -3.0 mmol/L                                                                                              | <lower limit of normal -3.0 mmol/L ; asymptomatic: treatment required                        | <3.0-2.5 mmol/L; hospitalization required                                           | <2.5 mmol/L; life-threatening                                                                 | Death |
| hyponatremia                           | <Lower limit of normal value -130mmol/L                                                                                               | --                                                                                           | <130-120mmol/L                                                                      | <120mmol/L; life-threatening                                                                  | Death |
| hypophosphate mia                      | < lower limit of normal - 2.5 mg/dL; < lower limit of normal - 0.8 mmol/L                                                             | <2.5-2.0 mg/dL; <0.8-0.6 mmol/L                                                              | <2.0-1.0 mg/dL; <0.6-0.3mmol/L                                                      | <1.0 mg/dL; <0.3 mmol/L ; life-threatening                                                    | Death |
| Decreased fibrinogen                   | <1.0-0.75 times lower limit of normal or 25% reduction from baseline                                                                  | <0.75-0.5 times lower limit of normal or 25% -<50% reduction from baseline                   | <0.5-0.25 times lower limit of normal or 50-<75% reduction from baseline            | <0.25 times lower limit of normal or 75% reduction from baseline, or absolute value <50 mg/dL | Death |

182

#### 183 4. Subject selection

##### 184 4.1 Inclusion criteria

185 (1) Patients diagnosed with acute leukemia and undergoing haploid hematopoietic stem cell

186 transplantation, regardless of gender, aged 18-60 years; KPS score > 60 points, expected survival >

187 3 months;

188 (2) Those who do not have serious damage to the function of important organs of the body;

189 (3) Signed the informed consent.

##### 190 4.2 Exclusion criteria

191 (1) Severe cardiac, renal or hepatic insufficiency;

- 192 (2) Combined with other malignant tumors that need treatment ;
- 193 (3) There are clinical symptoms of brain dysfunction or severe psychiatric disease that cannot be
- 194 understood or comply with the research protocol ;
- 195 (4) Those who cannot follow up as scheduled ;
- 196 (5) Patients who are not guaranteed to complete the required treatment plan and follow-up observation.

197 **4.3 Rejection or shedding criteria:**

198 During the treatment and follow-up period, disease changes or death unrelated to the experimental

199 factors occurred, and the observation could not be continued.

200 **4.4 Termination criteria:**

- 201 (1) Severe adverse reactions intolerable;
- 202 (2) The subject voluntarily requests to withdraw;
- 203 (3) Relapsed before receiving the MSC infusion;
- 204 (4) The investigators considered that the subjects were not suitable to continue treatment for other
- 205 reasons.

206

207 **5. Treatment options**

208 **5.1 GVHD Prevention**

209 (1) Experimental group: On the basis of conventional GVHD prevention, the experimental group was

210 re-infused with UC-MSCs 45 days after transplantation at a dose of  $1 \times 10^6$ /kg; infusion every two

211 weeks once, 4 times

212 (2) Control group: conventional GVHD prevention (Beijing program) (MMF) 0.5g q12h -7d~90d,

213 cyclosporine (CsA) 1.25mg/kg,; -1 day increment to 2.5mg/ kg; after the patient can tolerate it orally, it

214 is changed to 5 mg/kg orally, and the concentration is maintained at 200-300ng/ml; the dose is slowly

215 reduced 180 days after transplantation; methotrexate (MTX)  $15\text{mg}/\text{m}^2$  d1,  $10\text{mg}/\text{m}^2$  d3,6,11)

216 **5.2 Indicator observation**

- 217 (1) The incidence and severe chronic GVHD
- 218 (2) The overall incidence of chronic GVHD The incidence and severity of acute GVHD, OS ,
- 219 Post-transplant patient GRFS (GVHD-free and Relapse Free Survival)

220

221 **6. Research Process**

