## 148 **3. Clinical trial design**

### 149 **3.1 Overall Design**

150 A multicenter, randomized, controlled, open clinical trial was designed to explore the efficacy and  
 151 safety of umbilical cord-derived MSCs in preventing graft-versus-host disease after haploid  
 152 hematopoietic stem cell transplantation.

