265     After hematopoietic reconstruction to 1 year after transplantation, clinicians were blinded to the  
266     treatment allocation will access:

267     (1) Routine blood tests, liver and kidney function tests, CMV and EBV and other viral indicators (at  
268     least monthly)

269     (2) Bone marrow imaging, bone marrow biopsy (monthly)

270     (3) MRD, related gene mutation detection (monthly)7. Safety and Adverse Events

271     Safety will be measured and assessed daily by documenting potential adverse effects of treatment.  
272     Patients will be tested for potential toxicity that may arise from the treatment through tests such as  
273     medical history, physical examination, blood tests, etc.

274     **6.7 Recording of Adverse Events**

275     Investigators can gather information on adverse events through special questions or, in certain  
276     circumstances, tests in their interactions with each patient. All information about adverse events needs  
277     to be entered into the database immediately and into the Adverse Events module of the Case Report  
278     Form (CRF). All apparently relevant signs, symptoms, and abnormal diagnoses need to be entered into  
279     the database and grouped under the same diagnosis.

280     All adverse events that occurred during the study period were required to be recorded. All adverse  
281     events needed to be followed until resolved, stabilized, or until confirmed that study treatment or

282 participation was not an issue. Serious adverse events that persisted at the end of the study had to be  
283 followed until final results were determined. Any serious adverse events that occur after the study and  
284 that may be related to study treatment or study participation need to be recorded and reported promptly.  
285 If any subject has the following conditions within 2 weeks of receiving cell reinfusion therapy , the  
286 study will be required to be re-reviewed, and the clinical trial at this stage will be suspended:

- 287 (1) Respiratory failure requires artificial respirator.  
288 (2) Grade 4 (life-threatening) toxicity due to treatment regimen.  
289 (3) Death.

290

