## 329 **10. Subject management**

330 During the treatment period, the subjects will be followed up by a special investigator, and if they feel  
331 unwell, they can contact the investigator at any time to ensure the safety of the patients to the greatest  
332 extent.

333 The subject's treatment compliance includes the subject's consent to participate in the study, willingness  
334 to receive the prescribed drug treatment, and willingness to collect blood samples and bone marrow  
335 specimens to evaluate efficacy and safety. Subjects may be excluded from the study due to lack of good  
336 compliance with treatment or follow-up at the discretion of the sponsor and investigator.

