## 337 **11. Statistical Analysis Plan**

338 The Mann–Whitney tests, the chi-squared test, and Fisher's exact test were used to compare the AE  
339 between the MSC group and the control group. The competing risk model (Fine and Gray model) was  
340 used to estimate 2-year cumulative incidences and hazard ratios (HRs), with their 95% CIs, for severe  
341 cGVHD and cGVHD (competed by death and relapse) and leukemia relapse (competed by nonrelapse  
342 death). The cumulative incidence of grade II-IV aGVHD and grade III-IV aGVHD, the GRFS rate and  
343 the OS rate were estimated using Kaplan–Meier analysis and are expressed as percentages with 95%  
344 CIs. The Kaplan–Meier method, the log-rank test, and Cox proportional hazard models was used to  
345 compare the grade II-IV aGVHD and III-IV aGVHD, GRFS and OS curves between the two groups.  
346 All reported *P* values are two-sided. Statistical analyses were performed using STATA 17 (StataCorp.  
347 2021. Stata Statistical Software: Release 17. College Station, TX: StataCorp LLC)) and R (version  
348 4.4.2, R Foundation for Statistical Computing, Vienna, Austria).

349

350

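### Sections 4.3, 4.4(3) and 10 may let patients who die or relapse be removed after randomisation in an open trial, and no analysis set keeps them in

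*Combined protocol and SAP*

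**What the plan says.** Section 3.1 sets an open design: "A multicenter, randomized, controlled, open clinical trial was designed to explore the efficacy and" safety of the cells. Three rules can then take a patient out during treatment or follow-up:

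- Section 4.3 (Rejection or shedding criteria) has a single criterion, which begins "During the treatment and follow-up period, disease changes or death unrelated to the experimental" and continues "factors occurred, and the observation could not be continued".
- Section 4.4 (Termination criteria), item 3, reads "Relapsed before receiving the MSC infusion".
- Section 10 (Subject management): "Subjects may be excluded from the study due to lack of good" "compliance with treatment or follow-up at the discretion of the sponsor and investigator".

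Section 11 uses a Fine and Gray model for severe "cGVHD and cGVHD (competed by death and relapse) and leukemia relapse (competed by nonrelapse" death), and compares OS and GRFS between the arms by log-rank test and Cox model. Section 6.6 says of the monitoring tests: "After hematopoietic reconstruction to 1 year after transplantation, clinicians were blinded to the" allocation.

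No section defines an intention-to-treat or other analysis set, says how rejected, terminated or excluded patients are analysed, or says who decides that an event is unrelated.

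**The concern.** Death is an OS and GRFS event under section 11 and a competing event for the primary endpoint. Relapse is analysed in its own right, enters GRFS, and also competes with severe cGVHD. Section 4.3 makes a death attributed to other causes a ground for rejection. Its words on disease change could also cover relapse. If rejection means leaving the analysis, the events that section 11 needs go missing.

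The loss need not be equal across arms. Controls receive no MSC, so relatedness to the experimental factors does not mean the same thing for them. Section 4.4(3) refers to an infusion that only one arm receives. Only the MSC arm has four extra infusions with which to comply under section 10. In an open trial, attribution and compliance decisions that depend on arm can undo the comparability that randomisation gives.

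**Working it through.** **The plan's own figure.** This point rests on no printed number. The nearest is the loss allowance in section 8: 142 / (1 − 0.10) = 157.8, so 158, or 79 per arm. That reproduces. Exclusions after randomisation would draw on the same 158 − 142 = 16 patients.

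**The passages side by side.** There are three ways to handle a patient who dies of a cause judged unrelated:

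1. Deleted: the patient leaves the randomised comparison.
2. Censored at death: this contradicts the competing-event treatment in section 11 and is invalid for OS.
3. Kept and counted: this respects section 11, but nothing in the documents says so.

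The further condition in section 4.3, that observation could not go on, is always met by a death.

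**OS illustration.** The documents give no mortality or exclusion rates, so these are assumptions. True 2-year mortality D is equal in both arms, with 79 per arm, and a fraction f of the deaths in an arm is removed.

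- Apparent mortality = (D − fD) / (1 − fD)
- Apparent HR = ln(1 − MSC mortality) / ln(1 − control mortality)

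With D = 0.30 and f = 0.25 in the MSC arm: 0.225 / 0.925 = 0.243. With f = 0.50: 0.15 / 0.85 = 0.176. With no control deaths removed, HR = ln(0.757) / ln(0.70) = 0.78 and ln(0.824) / ln(0.70) = 0.54. The last column is the chance of a two-sided p below 0.05 when there is no true difference (two-proportion normal approximation).

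| D | MSC deaths removed | Control deaths removed | Apparent mortality, MSC / control | HR | Chance of p < 0.05 |
|---|---|---|---|---|---|
| 30% | 25% | 0% | 24.3% / 30.0% | 0.78 | 0.12 |
| 30% | 50% | 0% | 17.6% / 30.0% | 0.54 | 0.41 |
| 30% | 10% | 10% | 27.8% / 27.8% | 1.00 | 0.05 |
| 30% | 25% | 10% | 24.3% / 27.8% | 0.85 | 0.08 |
| 30% | 50% | 10% | 17.6% / 27.8% | 0.60 | 0.30 |
| 20% | 25% | 10% | 15.8% / 18.4% | 0.85 | 0.07 |
| 20% | 50% | 10% | 11.1% / 18.4% | 0.58 | 0.23 |

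**Primary endpoint, competing events removed.** Apparent incidence = true incidence / (1 − competing incidence × fraction removed). With the 15% control rate from section 8, an assumed 30% competing incidence and half of those patients removed: 0.15 / (1 − 0.30 × 0.50) = 0.15 / 0.85 = 17.6%. The denominator shrinks, so the affected arm looks worse.

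**Primary endpoint, event patients removed.** If the 5.7% and 15% of section 8 are read as end-of-study proportions, 79 × 0.057 + 79 × 0.15 = 4.5 + 11.9, or about 16 events in all. With a true 15%, one event patient excluded from an arm gives (11.85 − 1) / 78 = 13.9%; three give (11.85 − 3) / 76 = 11.6%.

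**The case against.** The best defence is that section 4.3 is only a disposition label for dropouts and that section 11 governs the analysis. On that reading nothing conflicts: section 10 speaks of leaving the study, not the analysis, and section 11 lists death and relapse as events. This stands to the extent that the text permits removal and does not order it. It does not close the gap, because no sentence says that such patients stay in.

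Several stronger readings are tempting but unsupported:

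- A reader might infer that deaths and relapses are in fact deleted. No section says so.
- A reader might infer that relatedness is assessed with allocation known. No section says who makes that assessment. The blinded clinicians of section 6.6 are not tied to these decisions, so they neither prove nor remove the risk.
- A reader might equate disease change with relapse. The term is undefined, and relapse before infusion has its own rule in section 4.4.
- A reader might infer a bias in favour of MSC. Removing MSC-arm deaths would flatter OS, but removing competing events from the same arm would raise its severe cGVHD incidence.
- A reader might think that losing 20% to 30% of the patients with competing events lifts 15% to 19–21%. Those figures need 20% to 30% of the whole arm to be removed (0.15 / 0.8 and 0.15 / 0.7). At a 30% competing incidence the result is 0.15 / 0.94 = 16.0% to 0.15 / 0.91 = 16.5%.

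Section 7 also does not say when randomisation happens relative to day 45. Section 4.4(3) matters here only for relapses between randomisation and first infusion.

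**Conclusion.** The concern holds as a matter of what the plan allows. Patients with deaths or relapses may be removed after randomisation, in an open trial, by rules that can work differently in the two arms, and no defined analysis set prevents it. This affects the primary endpoint, OS, GRFS and relapse, so it is more than a missing detail.

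The size and direction of bias cannot be fixed from the documents. An OS hazard ratio of 0.78 or 0.54 with no true difference requires 30% mortality, 25% or 50% of MSC-arm deaths removed and no control deaths removed. With 10% of control deaths also removed it is about 0.85 or 0.60. Equal proportional removal leaves the comparison close to unbiased when true mortality is equal, although both arms' mortality is understated. These are scenarios, not estimates of what happened.

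**What to change.** State in section 11 that:

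- the primary analysis set is all randomised patients in their assigned arm;
- sections 4.3, 4.4 and 10 may end study treatment or visits but remove nobody from the analysis;
- every death is an OS and GRFS event, every relapse is a relapse and GRFS event, and either one occurring before severe cGVHD is a competing event, whatever the attribution;
- outcome follow-up continues after study treatment stops;
- patients are censored only at withdrawal of consent, loss to follow-up or administrative end of follow-up;
- any per-protocol analysis is a sensitivity analysis only.

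The sample size stays at 158 and the two-sided error at 0.05. Clinical stopping rules are unchanged. The cost is wording plus some added follow-up of patients who stop study treatment. The documents do not show that outcomes are already collected after exclusion, so for anyone already excluded they may have to be retrieved.
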